### Addressing Aim 1: Target trial emulation

#### Target trial design

A hypothetical target trial will be emulated in which young men and women taking valproate would be randomised to either continue valproate, switch to lamotrigine or levetiracetam, or discontinue valproate [21]. The following mortality and morbidity outcomes would be assessed over the subsequent five years:

Deaths (all-cause/epilepsy-related);ED/hospital admissions (all-cause/epilepsy-related);Seizures (symptom codes);Falls;Injuries;Burns;Aspiration pneumonia;Manic/bipolar episodes;New-onset depression;Self-harm/suicide;A composite morbidity index incorporating seizures, injuries, admissions, depression.

Intention-to-treat (ITT) and per-protocol effects would be assessed between groups [21]. Analysis would take a time-to-first-event approach (Cox-proportional hazards model) for deaths, new-onset depression and composite morbidity. A recurrent events approach (e.g., Prentice-Williams-Peterson Total Time Model) would be taken for the remaining outcomes.

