#### Target trial emulation using observational data from TriNetX and CPRD

*Eligibility criteria*. Anonymised, person-level, electronic health data will be extracted from TriNetX and CPRD, linked across primary care, ED, inpatients, outpatients, and mortality subsets. The study period will be from 01/01/2014 to 01/01/2024. Included will be men and women aged 16–54 years. The study will take an open cohort design with patients entering the cohort when the following criteria are met:

Either: ≥1 epilepsy disease or symptom code recorded during the study period and two separate valproate prescription instances over the preceding 12 months before at least one of the epilepsy disease or symptom codes;

Or: ≥1 epilepsy disease or symptom code recorded any time before the study period with at least two separate valproate prescription instances over 12 months during the study period.

TriNetX and CPRD use ICD-10-CM and SNOMED codes, respectively. The coding strategy combining disease and symptom codes with valproate, as used our published study successfully [20], was shown to accurately identify epilepsy cases in our prior work [28,29].

Treatment arms:

Withdrawn valproate and commenced lamotrigineWithdrawn valproate and commenced levetiracetamWithdrawn valproate and no new ASM commencedContinues valproate

*Treatment assignment*. Baseline (time 0) will be defined as when valproate dose reduction commences (treatment arms 1–3) or prescription of valproate at a matched time (arm 4). Eligible individuals are assigned at baseline to the treatment strategy that their data are consistent with [21]. To emulate randomisation, adjustment is made for baseline confounders using Robins’ generalised methods (g-methods, e.g., inverse probability weighting) [21], considering age, sex, ethnicity, deprivation, type of epilepsy (using G40 codes), baseline seizure frequency (symptom codes recorded over preceding 12 months), alcohol excess, developmental delay, Cambridge Multimorbidity Score, length of valproate treatment, valproate dose, and ASMs used other than valproate. The final set of covariates required to adjust for confounding will be chosen using a causal directed acyclic graph [21].

*Outcomes*. These are listed in the target trial design section and derived from our prior work [1,20,30,31], and public consultation. All coded events will be recorded for flexible categorical or continuous analyses, as needed.

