### Addressing Aim 2: Causal prediction modelling

A causal prediction model will be created using Cox-proportional hazards of time-to-first-event in a causal framework [26]. The predicted outcome will be a composite personal harms risk combining epilepsy-related deaths, seizures, injuries, admissions, and depression. Predictors for definite inclusion in the final model will be treatment arms 1–4. Candidate predictors considered in addition will be taken from the list of baseline confounders adjusted in the target trial emulation, alongside any additional variables considered to influence outcome but not treatment assignment. *A priori* clinical expertise and data-driven variable selection will refine the predictor variable list for modelling [30]. Penalisation methods (e.g., *lasso*), will be used to combine variable selection with shrinkage (reducing overfitting risks).

The model will be developed in TriNetX to help ensure it is internationally generalisable [32]. External validation will be undertaken in CPRD, facilitating subsequent clinical implementation [32]. Internal validation within TriNetX will involve 1,000 bootstrap analysis samples. Nagelkerke’s R^2^ and Brier Scores will estimate overall model performance. Calibration will be estimated with calibration-in-the-large, calibration slope, and flexible calibration plots, and discrimination with C-index. Calibration and discrimination will be reassessed within CRPD to externally validate model performance [32]. Counterfactual prediction will be embedded into the model development [26], allowing patients and clinicians to answer clinically meaningful questions such as “at the point of proposed valproate withdrawal, accounting for baseline characteristics, what is the risk of epilepsy-related death or composite morbidity for levetiracetam? And what is it for lamotrigine?”

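### The named baseline covariates include prior history of only one study outcome (seizures); prior ED use, injuries, falls, self-harm and mood disorder should be named as candidate confounders

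*Protocol article*

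**What the plan says.** The protocol's section on emulation using TriNetX and CPRD lists the variables considered for baseline adjustment. They are age, sex, ethnicity, deprivation and epilepsy type, then "baseline seizure frequency (symptom codes recorded over preceding 12 months), alcohol excess, developmental delay, Cambridge Multimorbidity Score", then "length of valproate treatment, valproate dose, and ASMs used other than valproate". That makes twelve. The list is followed by: "The final set of covariates required to adjust for confounding will be chosen using a causal directed acyclic graph".

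The outcomes, under Target trial design, are deaths, ED and hospital admissions, "Seizures (symptom codes);Falls;Injuries;Burns;Aspiration pneumonia;Manic/bipolar episodes;New-onset depression;Self-harm/suicide" and a composite morbidity index. Deaths, new-onset depression and the composite are analysed as time to first event. A recurrent-events approach "would be taken for the remaining outcomes".

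For Aim 2, "Candidate predictors considered in addition will be taken from the list of baseline confounders adjusted in the target trial emulation". The only addition to that list is variables thought to affect outcome but not treatment assignment.

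The stand-alone outcome is new-onset depression. The composite in Target trial design and the composite in Aim 2 both say depression without the qualifier.

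**The concern.** The authors recognised that earlier seizures must be balanced when later seizures are the outcome, and they gave a look-back window for them. The same reasoning applies to the other morbidity outcomes. A patient's recent record of ED visits, falls, injuries, self-harm or mood disorder is likely to predict the same events later, and may also influence whether valproate is withdrawn. If such a history differs between arms 1–3 and arm 4 after adjustment for the printed list, the difference would appear in the results as harm or benefit of withdrawal.

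ED attendance is the outcome on which the sample size rests. The Aim 1 figures are intended for a national decision-support tool, and the Aim 2 model for public release.

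Aim 2 inherits the gap. A history that affects both treatment and outcome can enter the model only through the confounder list, because the extra variables are limited to those that do not affect assignment.

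A smaller, related point is that the two composites do not say whether a repeat code for old depression counts as an event.

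**Working it through.** **1. Outcomes set against covariates.**

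| Outcome | Own prior history named as a covariate? |
|---|---|
| Seizures | Yes, 12 months |
| ED/hospital admissions | No |
| Falls, injuries, burns | No |
| Aspiration pneumonia | No |
| Manic/bipolar episodes | No (perhaps partly in the multimorbidity score) |
| New-onset depression | No, but implied by the outcome's name |
| Self-harm/suicide | No (perhaps partly in the multimorbidity score) |

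The document does not give the components of the multimorbidity score.

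**2. The plan's own figure and the benchmark.** Table 1 gives ED attendance of 2977/8021 = 0.3712 (withdrawn) and 2471/8021 = 0.3081 (continuing). The difference is 0.0631 and the ratio 1.205. The printed formula gives (1.960 + 0.842)² × (0.2334 + 0.2132) / 0.0631² = 881 after rounding up, which reproduces the stated minimum. Nothing in this point changes it.

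**3. Bias on the difference scale.** Bias = residual imbalance in prior ED use × risk difference between prior attenders and others. The document supplies neither input. Assume a 5-year ED risk of 60% in prior attenders and 22% in others, a gap of 38 points.

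- 10-point imbalance (35% vs 25%): 0.10 × 0.38 = 0.038, or 3.8 points. This is 0.038/0.0631 = 60% of the pilot difference.
- 5-point imbalance: 0.05 × 0.38 = 0.019, or 1.9 points, 30% of the pilot difference.

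The implied risk in continuing patients is 0.22 + 0.25 × 0.38 = 31.5%, close to the pilot's 30.8%, so the scenario fits that figure.

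**4. Bias on the ratio scale, with milder cases.** With prevalence of the history q1 (withdrawn) and q0 (continuing), and risk ratio g for the outcome, the bias factor is B = (1 + q1(g−1)) / (1 + q0(g−1)). The last two columns give the approximate chance of a significant difference when withdrawal has no effect. They use 881 per group, and then the TriNetX figure of about 14,234 with a third withdrawn (about 4,745 vs 9,489). All of q0, q1 and g are assumed.

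| q0 | q1 | g | B | 881 per group | TriNetX size |
|---|---|---|---|---|---|
| 0.20 | 0.25 | 2 | 1.04 | 8% | 34% |
| 0.20 | 0.30 | 2 | 1.08 | 21% | 87% |
| 0.20 | 0.30 | 3 | 1.14 | 50% | >99% |
| 0.20 | 0.40 | 3 | 1.29 | 97% | >99% |

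On the log scale these are about 22%, 43%, 72% and 135% of the pilot ratio. A larger sample does not reduce the bias; it makes the bias more likely to reach significance.

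**5. Effect on the Aim 2 parameter count.** There are 12 listed covariates and 3 parameters for four arms. The fix adds 9 histories: six counts (ED attendances, admissions, falls, injuries, burns, aspiration pneumonia) and three prior diagnoses (depression, bipolar/manic disorder, self-harm). 12 + 3 + 9 = 24, even at one parameter each, against the 20 assumed.

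The 1,204 can be reproduced from Table 1. With rate 0.068 over 5 years, the null log-likelihood per person is 0.34 × ln(0.068) − 0.34 = −1.254. The maximum Cox-Snell R² is 1 − exp(−2.508) = 0.9186, and 15% of that is 0.1378. Then n = 20 / (0.1 × −ln(1 − 0.1378/0.9)) = 20 / 0.016617 = 1,204. With 24 parameters, 24 / 0.016617 gives about 1,445.

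**The case against.** The strongest reply is that the covariate list is provisional. The final set is to come from a causal diagram, and a journal article reasonably leaves the full weight model to an analysis plan. This stands in part. A reader might infer that the diagram can only prune the printed list, but no sentence says so, and it may add variables. Equally, nothing commits it to add these. The printed list is specific enough to give a look-back for seizures while passing over the other outcomes.

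Second, the listed covariates may already balance much of the missing history. Seizure frequency, alcohol excess, the multimorbidity score and other ASMs could all correlate with ED use and psychiatric history. This also stands. It is why bias is possible rather than certain, and why the figures that treat the imbalance as wholly residual are at the upper end. A summed score can, however, be equal in two patients whose histories of self-harm or falls differ.

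Third, a recurrent-events model might be thought to handle history. The example the protocol names orders events within follow-up, so it does not use what happened before time 0.

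Two stronger readings are not supported:

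- A reader might say that nothing removes patients with earlier depression from the stand-alone outcome. The term new-onset already implies their exclusion, although no rule is written. In the composites, depression may simply be shorthand for that outcome, so what remains is a clarification.
- A reader might extend the point to a biased lamotrigine-versus-levetiracetam comparison on mood and self-harm. The stated causal estimand compares arms 1–3 with arm 4, and the Aim 2 composite contains neither bipolar episodes nor self-harm.

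**Conclusion.** The gap is real and should be fixed. Of the outcomes studied, only seizures have their own prior history named among the covariates, and the rule for adding Aim 2 predictors does not make good the omission. Adjusting for the printed list alone could leave plausible common causes of withdrawal and later morbidity unbalanced.

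The size cannot be known from the document. Under the assumed inputs, the bias in ED attendance is 1.9 to 3.8 points against the pilot's 6.3. In the mildest ratio-scale case tabulated it is a factor of only 1.04. The pilot comparison was itself propensity-matched, so it serves as a yardstick and not as an estimate of this bias.

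A reader might conclude that the emulation fails for these outcomes, or that baseline differences will be reported as effects. That goes too far: it needs imbalance that survives the listed covariates and a diagram step that leaves these histories out, and the document establishes neither.

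**What to change.** Name the following as prespecified candidate confounders entering the causal diagram and the weight model, and hence the Aim 2 candidate list:

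- 12-month pre-baseline counts of ED attendances, admissions, falls, injuries, burns and aspiration pneumonia;
- any prior depression, bipolar or manic disorder, and self-harm.

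State that the risk set for new-onset depression excludes patients with a depression code before time 0. Use that same definition for the depression component of the Target trial design composite and the Aim 2 composite.

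The cost is mainly analysis work, since the codes are already needed to define the outcomes. The weight model becomes larger. The Aim 2 budget rises to at least 24 candidate parameters, so the 1,204 must be restated: about 1,445 if Table 1's other assumptions are kept, and more if any variable needs several parameters. The roughly 14,234 patients in TriNetX should still suffice. The 881 does not change.

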*Causal estimand*: Assesses impact of treatment arms 1–3 vs. 4 on outcome (per-protocol assumption as observational data limits ITT assessment) [21].

*Start and end of follow-up*. The start of follow-up (Time 0 or index date) will be defined as when valproate treatment discontinued (treatment arms 1–3) or prescription of valproate at a matched time (arm 4). For time-to-first-event analyses, the end of follow-up will be defined as when the outcome occurs, censoring (including deviation from assigned treatment or leaving the study catchment area), or 10 years. For recurrent events analyses, alongside censoring as above, the end of follow-up will be 10 years, allowing for all events to be assessed throughout follow-up.

*Statistical analysis*: mirrors target trial section.

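### Neither stated time 0 keeps the newly started drug out of the baseline covariates, and reading covariates at discontinuation would also admit taper doses and taper seizures

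*Protocol article*

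**What the plan says.** All of this is in the protocol article, Methods, section on target trial emulation using TriNetX and CPRD, unless stated otherwise.

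- **Treatment assignment, date:** "Baseline (time 0) will be defined as when valproate dose reduction commences (treatment arms 1–3) or prescription of valproate at a matched time (arm 4".
- **Treatment assignment, adjustment:** "adjustment is made for baseline confounders using Robins’ generalised methods (g-methods, e.g., inverse probability weighting". The covariates listed include "baseline seizure frequency (symptom codes recorded over preceding 12 months" and "length of valproate treatment, valproate dose, and ASMs used other than valproate". Dose and other ASMs have no measurement window of their own.
- **Treatment assignment, selection:** "The final set of covariates required to adjust for confounding will be chosen using a causal directed acyclic graph".
- **Treatment arms:** arms 1 and 2 combine withdrawal of valproate with the start of lamotrigine or levetiracetam. The order of the two steps is not fixed.
- **Start and end of follow-up:** "The start of follow-up (Time 0 or index date) will be defined as when valproate treatment discontinued (treatment arms 1–3".
- **Aim 2 (causal prediction modelling):** candidate predictors come from the same confounder list, and the model is meant for use "at the point of proposed valproate withdrawal, accounting for baseline characteristics".

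**The concern.** A baseline confounder must be measured before the treatment strategy begins. A switch has two components, starting a new drug and lowering valproate, but both time-0 definitions look at valproate only. A covariate read at time 0 can therefore already reflect the switch.

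Three covariates are exposed:

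- **Other ASMs** may include the drug that defines arm 1 or arm 2.
- **Valproate dose** may be a taper dose in arms 1–3, set against an ongoing dose in arm 4.
- **The 12-month seizure count** may include seizures that occurred during the taper.

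The first two would nearly identify the arm, which threatens positivity and produces extreme weights. The third is an early effect of withdrawal, and adjusting for it can remove part of the harm the study wants to measure. The Aim 2 model could also be trained on values that differ from those available when a clinician would use it.

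**Working it through.** **1. Plan figures.** The article gives no figure on this point. Its sample sizes do not depend on it, and both reproduce. With p1 = 2977/8021 = 0.3712 and p2 = 2471/8021 = 0.3081, the formula in Table 1 gives (1.960 + 0.842)² × (p1q1 + p2q2)/(p1 − p2)², which rounds up to 881. Rate 0.068, 5 years, 15% of the maximum Cox–Snell R² (0.9186), 20 parameters and shrinkage 0.9 give 1,204.

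**2. The two dates side by side.** For anyone who is tapered, discontinuation comes after the start of reduction.

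| Covariate | Read at start of reduction | Read at discontinuation |
|---|---|---|
| Other ASMs | Contains the arm's drug if it was started first | Contains the arm's drug if it was started before valproate stopped |
| Valproate dose | Pre-taper, unless taken from the first reduced prescription | End-of-taper dose in arms 1–3, ongoing dose in arm 4 |
| 12-month seizure count | Ends before the taper | Includes the taper |

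The first row is exposed under both dates. The other two are exposed, in the main, only under the second.

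**3. Share of the seizure window (assumed tapers).** 3/12 = 25% for a 3-month taper and 6/12 = 50% for a 6-month taper in arms 1–3. In arm 4 it is 0%.

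**4. Weights if the arm's drug enters the covariate (assumed shares).** Suppose 90% of arm 1 and 5% of arm 4 have a recent lamotrigine start before time 0. Compare arm 1 with arm 4, using unstabilised weights.

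- Equal arms: P(arm 1 | start) = 0.90/(0.90 + 0.05) = 0.947. The weight for an arm 4 patient with a start is 0.95/0.05 = 19.
- Table 1 puts the withdrawn share at about a third. If that splits evenly over arms 1–3, arm 1 is 1/9 and arm 4 is 6/9, a ratio of 1:6. The weight for an arm 4 patient with a start is (0.90 + 6 × 0.05)/(6 × 0.05) = 1.20/0.30 = 4. The weight for an arm 1 patient without one is (0.10 + 6 × 0.95)/0.10 = 5.80/0.10 = 58.

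Unequal arms move the extreme weights to a different cell; they do not remove them.

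**5. Seizure count containing the taper (simulation, all inputs assumed).** The simulation had 1,000,000 patients per scenario, with gamma-distributed seizure rates (shape 0.7, mean 1 per year). Withdrawal multiplied the rate from the start of the taper. The outcome was the seizure count over one year after discontinuation, with inverse probability weighting on the 12-month count alone. Log-odds of withdrawal were −1, or −1 + 0.3 × prior count (capped at 6) when confounded. With the count taken before the switch, the estimates recovered the truth (1.247–1.251, 1.491–1.507 and 1.997–2.007). With the count taken at discontinuation:

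| Switching depends on prior seizures | True rate ratio | 1-month taper | 3-month taper | 6-month taper |
|---|---|---|---|---|
| No | 1.25 | 1.23 | 1.21 | 1.17 |
| No | 1.5 | 1.47 | 1.39 | 1.31 |
| No | 2.0 | 1.91 | 1.74 | 1.55 |
| Yes | 1.25 | 1.25 | 1.25 | 1.26 |
| Yes | 1.5 | 1.48 | 1.45 | 1.42 |
| Yes | 2.0 | 1.93 | 1.81 | 1.66 |

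In the confounded 1.25 case, residual confounding offsets the attenuation.

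**The case against.** The paragraph that lists the covariates also defines baseline as the start of dose reduction. On a plain reading, dose and the 12-month count are then taken before the taper. The later date stands under start and end of follow-up, and nothing there says that covariates are measured on it. If covariates are read at reduction and follow-up starts at discontinuation, the fault is a different one: events during the taper are missed, and patients are selected for having come through it. The Aim 2 wording also agrees with a pre-taper baseline. **This stands.** A reader might infer that the plan as written adjusts for taper doses and taper seizures. The text does not support that; it holds only if covariates are read at discontinuation.

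A second objection is that a causal diagram will choose the final covariates, and that look-back windows belong in an analysis plan or code list not shown here. **This stands only in part.** The diagram could drop or redefine a covariate. But prior dose, other ASMs and seizure frequency are plausible confounders when measured before the switch, so a sound diagram would tend to keep them. Choosing variables does not set their dates. The article does set dates, two of them, and both ignore the start of the new drug.

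A third objection is that the documents never say the replacement is started before valproate is lowered. **This is correct**, so the problem with other ASMs is conditional too. The arm definitions leave that order open, and nothing excludes the arm's drug from the covariate.

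**Conclusion.** The point holds in a limited form. The two definitions of time 0 conflict for anyone tapered. Under either, the covariate for other ASMs can contain the arm-defining drug when that drug was started before the chosen date. Contamination of valproate dose and the seizure count, and most of the mismatch with Aim 2, follows only from reading covariates at discontinuation.

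The size cannot be derived from the documents. Under the assumed inputs, a 3-month taper moves a true rate ratio of 1.5 to 1.39 without confounding and to 1.45 with it. In the simulated scenarios any material shift is towards understating the harm of withdrawal, but a shift does not always appear. The weights of 19, 4 and 58 rest on assumed shares of 90% and 5% and on assumed arm sizes. They show how a positivity problem could arise and are not predictions. It would be too strong to say that the weights will be undefined, or that the adjustment as planned does condition on treatment and its effects.

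**What to change.** Reconcile the treatment assignment and follow-up paragraphs to a single analytic time 0, used for eligibility, assignment, covariates and start of follow-up. Place it at the first recorded switching step: the first prescription of the new ASM or the first valproate reduction, whichever is earlier, and the matched date in arm 4. This sets an analysis date only and says nothing about how a switch should be carried out.

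Then state that:

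- valproate dose, other ASMs and the 12-month seizure count are measured strictly before that date;
- a drug started as part of the switch is treatment and is excluded from the baseline ASM covariate;
- the same pre-switch values are the inputs to the Aim 2 model.

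Closing the covariate window earlier is not enough by itself. If follow-up still began at discontinuation, events during the taper would stay uncounted.

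The cost is some extra date logic in the extraction code and no new data. Prescription records will misdate the first switching step for some patients. At that step a patient's record may still fit more than one arm. This is already so at the start of dose reduction, and the assignment rule for such patients should refer to the same date.

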We recently published a study of 8,991 men and 5,243 women aged 16–54 with epilepsy taking valproate in TriNetX [20]. This was a survival analysis assessing 5-year mortality and morbidity in those withdrawn from valproate between 01/06/2015–01/06/2018 (regardless of whether switched to another ASM), with propensity-matched comparisons to those who remained on valproate. Results suggested substantially increased risks of emergency department (ED) attendances, hospital admissions, falls, injuries, burns and new-onset depression in both men and women withdrawn from valproate [20]. However, these were aggregate data designed to scope potential trends and generate hypotheses, not to probe causal links.

To progress the field, we propose a comprehensive study examining mortality and morbidity outcomes in individuals who either continued valproate, switched to lamotrigine or levetiracetam, or discontinued valproate. Employing a novel approach known as target trial emulation [21,22], this study will replicate a hypothetical randomised-controlled trial (RCT) using person-level retrospective observational data from both TriNetX and Clinical Practice Research Datalink (CPRD, which encompasses 60m UK patients) [23]. Target trial emulation minimises confounder and selection biases in observational studies by statistically emulating randomisation at baseline (time 0) [21]. Individuals are then analysed based on the treatment strategy aligned with their data. Results are available quickly and shown to mirror those of an RCT [21]. This offers a cost-effective and immediate alternative to conducting an RCT [21]; crucial given the urgency for information on valproate withdrawal safety amidst ongoing regulatory changes [24,25]. Additionally, the emulation facilitates creation of causal prediction models [26]. These are developed using observed data alongside causal theory and assumptions to calculate predicted risk under different hypothetical treatment conditions, allowing “what if” questions to be addressed for each potential (counterfactual) outcome [26]. This facilitates actionable prevention [26].

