### Benefits to PWE

This study will benefit PWE as substantial numbers of young men and women may soon be invited by their clinicians to come off valproate owing to both current and new regulatory changes [5,6]. Whilst this is justified in terms of preventing teratogenic harm, the patients will wish to know what the risks of withdrawing from valproate are for their own health [24,25]. This study will provide immediate evidence to help doctors answer that question [10]. It will also help patients make safer decisions over switching to alternative ASMs by generating the first ever causal prediction tool for this purpose [26]. This will be the largest study of valproate withdrawal to date, the first to assess risks in men and first to assess multiple outcomes beyond seizures alone for both men and women [11–17]. These outcomes will be collaboratively chosen with PWE through public engagement strategies, ensuring their relevance and impact on those most affected. Finally, mortality prediction is highlighted as a key recommendation for epilepsy research by NICE [27], meaning the causal prediction model generated by this study also addresses an established research need for PWE.

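### Two entry rules for arms 1–3 leave open whether a lapse in prescriptions counts as withdrawal, so arm 3 may mix planned stopping with non-adherence

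*Protocol article*

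**What the plan says.** All of the design text below is in the protocol article, under the section on target trial emulation using TriNetX and CPRD.

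- Treatment assignment sets baseline for arms 1–3 "when valproate dose reduction commences (treatment arms 1–3").
- Start and end of follow-up sets time 0 for the same arms "when valproate treatment discontinued (treatment arms 1–3").
- Arm 4 is dated, in both places, from a valproate prescription at a matching time.
- Arms 1 and 2 need a new drug to be started. Arm 3 is withdrawal with no new drug.
- Membership follows the record: "Eligible individuals are assigned at baseline to the treatment strategy that their data are consistent with".
- The candidate confounder list closes with "length of valproate treatment, valproate dose, and ASMs used other than valproate". It names no measure of adherence, prescription gaps or reason for stopping. The final set is left to a causal diagram.

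The intended use is stated elsewhere. Benefits to PWE speaks of people "invited by their clinicians to come off valproate". The Aim 2 section frames the prediction "at the point of proposed valproate withdrawal". Pathways to impact says that the Aim 1 figures are meant for a national decision support tool.

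**The concern.** The two time 0 rules differ in whom they admit as well as in date. A step-down must be visible in the record under one; under the other it is enough that valproate ends. No sentence separates a stop agreed with a clinician from a patient who no longer obtains the drug. These are different versions of the treatment, and people who lapse may differ in risk for reasons that have nothing to do with a planned stop.

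If lapses enter, they gather on one side of the comparison. Those with no new drug fit arm 3 only, whereas arm 4 members are obtaining valproate at time 0 by construction. At stake are the contrast of arm 3 with arm 4 and the ranking of arm 3 against arms 1 and 2. The same classification carries into Aim 2, because all four arms are fixed predictors in the model.

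**Working it through.** **Who enters under each rule**

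| Record | Dose-reduction rule | Discontinuation rule |
|---|---|---|
| Recorded step-down, then stop | Enters at the step-down | Enters at the stop |
| Prescriptions cease, no step-down, no new drug | No time 0 | Can enter arm 3 |

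Two other features bear on this. Eligibility asks for only two valproate prescriptions over 12 months, so intermittent users can qualify. A lapse in arm 4 is plausibly a deviation from assigned treatment and would be censored, while under the discontinuation rule the same behaviour can define entry to arm 3.

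**The plan's own figures (Table 1)**

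The pilot proportions with an emergency department attendance are 2977/8021 = 37.12% (withdrawn) and 2471/8021 = 30.81% (remaining on valproate), a difference of 6.31 points. The printed formula, (1.960 + 0.842)² × (0.3712 × 0.6288 + 0.3081 × 0.6919) / 0.0631², gives 880.73 from unrounded inputs, so 881, which by this formula is a number per group. The stated 881 reproduces. It neither supports nor weakens the point; it supplies the scale.

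**Illustration 1: lapses have a higher risk than planned stops**

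Let q be the share of lapses in the arm and RR their risk relative to planned stops. Neither is in the documents; both are assumed. The observed risk is the planned-stop risk × (1 + (RR − 1)q), so:

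overstatement = 37.12 × (1 − 1/(1 + (RR − 1)q))

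- RR 1.5, q 0.2: 37.12 × (1 − 1/1.10) = 3.4 points
- RR 1.5, q 0.4: 37.12 × (1 − 1/1.20) = 6.2 points
- RR 1.25, q 0.2: 37.12 × (1 − 1/1.05) = 1.8 points
- RR 1.25, q 0.4: 37.12 × (1 − 1/1.10) = 3.4 points
- RR 1, any q: 0

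The most adverse of these would absorb nearly all of the 6.31-point difference.

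**Illustration 2: lapses have a larger excess over continuing valproate**

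Let f be the share of lapses and k the ratio of their excess risk to that of planned stops, again assumed. Then planned difference = 6.31 / ((1 − f) + fk).

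- f 0.1, k 2: 6.31/1.1 = 5.73 points
- f 0.3, k 2: 6.31/1.3 = 4.85 points
- f 0.5, k 3: 6.31/2.0 = 3.15 points
- k 1, any f: 6.31 points

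Over f 0.1–0.5 and k 2–3, the pooled difference is 1.1 to 2.0 times the planned one. The two illustrations make different assumptions and give different sizes. Neither is an estimate.

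**The case against.** A reader might infer that arms 1–3 accept any discontinuation and that the results will therefore not give the risk of a planned withdrawal. The document does not support that. The wording comes from a sentence on when the clock starts, and the treatment-assignment text ties entry to a dose reduction, which would leave out many abrupt stops. The extent of the problem turns on which text governs, and the article does not say.

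Other points on that side:

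- **Operational detail.** How a stop is recognised in the records may sit in a fuller document, and the data management plan promises public code. This stands for gap lengths and code lists. It does not cover two conflicting rules that are both printed.
- **Covariates.** The list includes plausible correlates of adherence, such as alcohol excess, deprivation, developmental delay, multimorbidity and length of treatment, and the causal diagram could add adherence. This stands as mitigation, but nothing commits to it. Adjustment also cannot by itself turn an unplanned stop into a planned one.
- **Safeguards.** Two prescriptions are required, and a patient who resumes valproate would be censored. Both limit the problem without removing it.
- **The 37.1%.** The pilot took withdrawn patients "regardless of whether switched to another ASM", so the figure pools switchers and non-switchers. This stands.
- **Aim 2 example.** It asks about levetiracetam and lamotrigine, not arm 3. True, but arm 3 is still a fixed predictor and an Aim 1 contrast.
- **Restricting the main analysis.** Admitting only stops with evidence of planning, and counting a replacement prescription as such evidence, would pass arms 1 and 2 almost automatically, filter arm 3 harder, and might condition on events after time 0. This stands, and that remedy is not proposed here.

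**Conclusion.** The point holds in a limited form. The two passages give different entry rules for arms 1–3. Under the discontinuation rule, lapses without a step-down can enter as withdrawal and, with no new drug, fall into arm 3. No named covariate measures prior adherence, and the figures are meant for people deciding on a proposed withdrawal. The arm 3 results may therefore overstate the harm of that withdrawal.

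The size cannot be derived from the documents. It depends on the share of lapses and on their excess risk, neither of which is given. The illustrations run from zero, if both kinds of stop carry equal risk, to 6.2 points on a stand-in risk of 37.1%. They credit nothing to covariate adjustment. The upward direction assumes that lapses carry the higher risk; if they carry a lower one, it reverses. That lapses concentrate in arm 3 is an inference from the arm definitions, with no figure behind it.

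**What to change.** 1. Reconcile the treatment-assignment and follow-up texts into one entry rule and one time 0 for arms 1–3, and state how a lapse in prescriptions without a recorded step-down is handled.
2. Add valproate prescription coverage over the 12 months before time 0 to the baseline confounders.
3. Prespecify a sensitivity analysis that separates stops with a recorded step-down or a recorded decision to stop from those seen only as a lapse. Apply the same criterion to all three withdrawal arms, use only information available by time 0, and do not count a replacement prescription as evidence of planning.

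The cost is a change of wording, one more derived covariate and one more analysis. Some planned stops will be misclassified as lapses where dose or decision codes are missing, so the two subgroups should be read with that in mind. The study status section says that data access permissions are still being sought, so the change can be made before any data are seen.
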